### Present study

#### The objectives of the present study are to investigate

i.Whether chemotherapy is related to long-term attenuation of gut microbiota alpha diversity (i.e. gut dysbiosis, and which species differ significantly between patients and healthy controls);ii.Associations between gut microbiota, body composition (i.e. fat mass and lean mass, body fat percentage, and bone mineral concentration), inflammatory cytokine biomarkers (IL-6, IL-1B, TNF-a, IL-10), C-reactive protein (CRP), lipopolysaccharide (LPS), serotonin (5-HT), brain derived neurotrophic factor (BDNF), and cortisol;iii.Associations between gut microbiota, and psychological and cognitive outcomes including anxiety, depression, PTSD symptoms, pain, fatigue, and social and cognitive functioning;iv.Relationships between demographic and clinical factors, gut microbiota, and physiological, psychological and cognitive outcomes for survivors.

We hypothesize that:
i.Chemotherapy will be associated with significant reductions in gut microbiota alpha diversity at all time points, and relative to healthy controls;ii.Gut dysbiosis will be associated with increased risk for overweight/obesity, elevated pro-inflammatory cytokines, CRP and LPS, reduced serotonin and BDNF, and augmented levels of cortisol in survivors;iii.Gut dysbiosis will be associated with increased anxiety, depression, PTSD symptoms, pain, fatigue, and social and cognitive deficits in survivors;iv.There will be relationships between certain clinical factors (e.g. mucositis, antibiotic use), gut microbiota alpha diversity, and physiological, psychological and cognitive outcomes.

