##### Sample size and power

Target sample sizes of at least *n* = 50 cancer survivors and *n* = 50 healthy controls were selected based on sample sizes from previous studies on gut microbiota in cancer patients [17, 18] and practical considerations given the timeline and availability participants. With this sample size (*n* = 100 total), a medium effect size for group differences (Cohen’s d = 0.5, estimated with a power of 0.80, alpha = 0.05) can be detected using a one-sided test of the primary hypothesis that cancer survivors will have lower alpha diversity relative to controls [46].

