### Procedure

Once identified, participants will be contacted by telephone or email to further verify inclusion and exclusion criteria, to obtain written informed consent, and schedule their first appointment. We will aim to assess participants at 3 different time points: < 2 months (T1), 3/4 (T2) and 5/6 (T3) months post chemotherapy, with healthy controls ideally being tested on the same day or within 5 days from when the patient is tested.

Participants will then receive a package via mail or in person, with instructions and materials for stool sample collection, and a link to fill out the self-report questionnaires, and demographic and clinical data online using REDCap. REDCap is a free, secure, browser-based application designed to support Electronic Data Capture for research studies provided through the Clinical Research Unit in the Cumming School of Medicine at the University of Calgary. Medical charts will also be accessed to confirm information regarding cancer diagnosis, treatment, glucocorticoid and antibiotic medication use, and mucositis.

Participants will be instructed to collect stool samples at home which can be stored in a freezer up to 3 days prior to their appointment, and to complete their online questionnaires prior to the appointment. On the day of their appointment, we will collect their stool sample from them. Participants will then be taken to have a hair sample collected for cortisol analysis (approximately 10 min), complete the cognitive task (i.e. the SART) on a computer (approximately 6 min), and complete their DXA scan (approximately 10 min), and have their blood drawn for serum biomarker analyses (approximately 10 min). This whole process should take approximately 45 min. Participants’ T2 and T3 month follow-up appointments will be scheduled at each subsequent visit and the procedure will be the same with respect to psychological and cognitive measures completed online, followed by their in person testing and biological sample collection. Participants will be provided a voucher for parking, and may choose from compensation in the form of either $30 at the end of the study or a pass to a fitness class after each appointment (they will have options to choose from in advance). If desired, participants will also receive a package with their individual results summarized and interpreted at the end of the study.

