### Data analysis

*Objective 1* will examine whether chemotherapy is related to long-term gut dysbiosis as indicated by reduced alpha diversity in patients relative to controls, and from time points 1 through 3. Gut microbiota alpha diversity will be evaluated with the Shannon and Chao1 indexes using QIIME. To further examine differences in bacterial composition between the groups, LEfSe (linear discriminant analysis effect size) will be used to evaluate differential abundance between patients and controls, allowing us to identify the key bacteria that contribute most to the chemotherapy group having different bacteria relative to healthy controls. Linear Mixed Modelling (LMM) analyses will be used to examine differences across time and between groups. Group (survivors vs. healthy controls) and time (T1 – T3) will be fixed factors and individual subject will be a random factor.

*Objective 2* will first test group differences in gut microbiota, cytokines, LPS, 5-HT and BDNF, cortisol, and body composition using LMM as described above. We will test the interplay between the physiological systems of our model by examining associations between the gut microbiota, cytokines, LPS, 5-HT and BDNF, cortisol, and body composition using univariate correlations. Then multivariate regression models regressing cytokines, cortisol and body composition on gut microbiota diversity will be conducted, including variables that showed significant univariate correlations in the modelling. Covariates included theoretically based on the literature will include type of cancer diagnosis (i.e. blood or solid tumor), history of mucositis, glucocorticoid medication, antibiotic, and probiotic use, birth delivery mode, and breastfeeding in infancy.

*Objective 3* will first test group differences in cognitive and psychological parameters, gut microbiota diversity, and levels of 5-HT and BDNF using LMM as described above. We will test the relationships between gut microbiota, 5-HT and BDNF, and cognitive and psychological parameters using univariate correlations. Then multivariate regression models regressing psychological and cognitive parameters on gut microbiota diversity will be conducted, including variables that showed significant univariate correlations in the modelling. Covariates included theoretically based on the literature will as specified in objective 2.

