*Objective 4* will explore relationships between clinical factors and all dependent variables, first using univariate correlations, followed by multivariate regression modelling to examine associations between cancer survivors’ clinical and demographic factors, and the dependent variables of gut microbiota alpha diversity and differential species composition, physiological parameters (i.e. cytokines, LPS, 5-HT, BDNF, and cortisol), body composition, and psychological and cognitive outcomes.

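### Objectives 2 and 3 let univariate significance choose regression variables and give no within-subject term for three visits; the Objective 2 regression leaves out LPS, serotonin and BDNF, and CRP is in no analysis step

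*Protocol article*

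**What the plan says.** All references are to the protocol article.

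- **Data analysis, Objectives 2 and 3.** Each objective has three steps: group differences by linear mixed model (LMM) with subject as a random factor, then univariate correlations, then regressions on gut diversity, "including variables that showed significant univariate correlations in the modelling". A further set of seven covariates is chosen on theory: cancer type, mucositis, glucocorticoids, antibiotics, probiotics, birth delivery mode and breastfeeding. No threshold for the screen is given.
- **Data analysis, Objective 2, regression outcomes.** "multivariate regression models regressing cytokines, cortisol and body composition on gut microbiota diversity will be conducted". LPS, serotonin and BDNF appear in the group LMM and in the correlations, but not here. CRP appears in none of the steps.
- **Present study, hypothesis (ii).** Besides overweight/obesity, it predicts "elevated pro-inflammatory cytokines, CRP and LPS, reduced serotonin and BDNF, and augmented levels of cortisol in survivors".
- **Procedure.** "We will aim to assess participants at 3 different time points". The LMM that handles these visits is invoked for group differences only.
- **Data analysis, Objective 4.** The order is "first using univariate correlations, followed by multivariate regression modelling", with no statement that significance decides entry.
- **Sample size and power.** The power statement ("Cohen’s d = 0.5, estimated with a power of 0.80, alpha = 0.05") concerns the alpha-diversity comparison only.

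**The concern.** Three features of the association analyses bear on what can be reported.

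1. **Entry by significance.** A variable that passes a 5% test and is then tested in the same data will usually pass again, whether or not the association is real. Confounders are affected too. The Demographics and clinical data section counts diet, exercise, bowel habits and smoking among the factors that influence the gut microbiota, yet none is on the theory-based list. They can enter only by reaching significance in a small sample, or not at all. The adjustment set would then differ from outcome to outcome.
2. **Repeated visits.** Correlation and ordinary regression have no term for repeated measurements of one person.
3. **Outcome list.** The regression does not cover what hypothesis (ii) predicts.

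The Discussion says that the study should validate aspects of the proposed model and inform interventions. The associations between gut, biomarkers and symptoms are the evidence for that, and as planned their uncertainty could be understated.

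**Working it through.** **Inputs from the document.** "Target sample sizes of at least *n* = 50 cancer survivors and *n* = 50 healthy controls"; d = 0.5, one-sided alpha 0.05; three visits; seven theory-based covariates. **Assumed, because the document gives no values:** the within-subject correlation (ICC), the number of candidate variables screened per outcome, the strength of confounders, and a screening threshold of 0.05.

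**Step 1: the plan's own figure.** Power = Φ(d·√(n/2) − 1.645) = Φ(0.5·√25 − 1.645) = Φ(0.855) = 0.804 (0.799 with the t distribution), against the stated 0.80. It reproduces. It concerns Objective 1 only; no power or error rate is stated for Objectives 2 and 3.

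**Step 2: what the screen does.** Simulation with 50 survivors, one visit and no true association: screen by correlation at p < 0.05, then fit a least-squares regression.

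| Candidates | Forced covariates | Screened-in null variable significant again | At least one false finding | Same number of independent tests, no screen: 1 − 0.95^k |
|---|---|---|---|---|
| 8 | none | 90% | 0.33 | 0.34 |
| 12 | none | 86% | 0.44 | 0.46 |
| 20 | none | 79% | 0.62 | 0.64 |
| 2 | 7 | 61% | 0.06 | 0.10 |
| 8 | 7 | 62% | 0.23 | 0.34 |
| 13 | 7 | 58% | 0.33 | 0.49 |

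The third column shows that the p-value after selection is not a 5% test. The last two columns show that the screen does not raise the overall count of false findings at a single visit. Without forced covariates, the unconditional error per candidate is 0.040–0.045.

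**Step 3: effect on the diversity coefficient.** Diversity is forced in and has no true effect; four confounders have assumed path coefficients of 0.2–0.3; one visit.
- All four confounders prespecified: type I error 0.055–0.057.
- Confounders kept only if significant: 0.08–0.12.

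This applies to confounders outside the theory-based list, not to those on it.

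**Step 4: three visits pooled as independent rows.** For a correlation of two variables with equal ICC, the design effect is 1 + 2·ICC², and the actual error of a 5% test is 2·[1 − Φ(1.96/√design effect)].

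| ICC | Design effect | Actual type I error |
|---|---|---|
| 0.3 | 1.18 | 0.071 |
| 0.5 | 1.50 | 0.110 |
| 0.7 | 1.98 | 0.164 |
| 0.8 | 2.28 | 0.194 |

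Simulation gives 0.079, 0.116 and 0.164 for ICC 0.3, 0.5 and 0.7. Prespecifying all confounders but still pooling visits at ICC 0.5 leaves an error of 0.10–0.11 for the diversity term. Correcting the covariate rule alone is therefore not enough.

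**Step 5: the alternative, visit by visit.** The outcomes are 4 body composition + 4 cytokines + CRP, LPS, serotonin, BDNF and cortisol = 13, and 7 questionnaires + the attention task (counted once) = 8, so 21. With one diversity index that is 21 tests, or 21 × 3 = 63 over three visits. The expected number of false positives at 5% rises from 1.05 to 3.15. Steps 4 and 5 are alternatives; both cannot apply.

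**Step 6: hypothesis (ii) against the Objective 2 steps.**

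| Outcome | Group LMM | Correlation | Regression on diversity |
|---|---|---|---|
| Cytokines, cortisol, body composition | yes | yes | yes |
| LPS, serotonin, BDNF | yes | yes | no |
| CRP | not named | not named | not named |

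**The case against.** **Several stronger readings are tempting, and the document does not support them.**

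- *That Objective 4 uses the same screen.* It gives an order of steps, not a selection rule.
- *That the chance of a false finding in Step 2 (33% with 13 candidates) measures harm from screening.* Thirteen unscreened independent tests would give 49%. That figure is ordinary multiplicity, and the two-step procedure lowers it. What is lost is the meaning of p-values after selection.
- *That the main confounders may be dropped.* Seven covariates are listed on theory and appear to enter regardless. Since the regressions are on diversity, it reads as the named predictor, although the text does not say whether it must itself pass the screen.
- *That controls are pooled into these regressions.* Nothing says so. Hypotheses (ii) and (iii) concern survivors, and cancer type as a covariate points to survivor-only models.
- *That hypothesis (ii) goes untested for all four markers.* LPS, serotonin and BDNF have a group comparison and a correlation with gut microbiota. They lack only an adjusted test against diversity.

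**Further points on the other side.** A condensed article may leave the handling of visits to a fuller document, and pooling is an inference. That stands, so the 7–19% is conditional. The text does, however, attach the subject random factor to group differences and then names methods that have none. CRP shares a paragraph and an assay with the cytokines in the Biomarker outcomes section, so it may be meant under that word; but the objectives and hypothesis (ii) list it separately. The study also calls itself exploratory. That limits the weight of the point, but the hypotheses are directional and the rule is cheap to replace.

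**Conclusion.** The point holds in limited form and should be corrected.

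- In Objectives 2 and 3, p-values for screened-in variables do not have their nominal meaning: a null variable that passes the screen is significant again 58–90% of the time under the assumed settings. Confounders outside the theory-based list are adjusted for only if they happen to reach significance; for such confounders, assumed strengths give 8–12% error for diversity instead of about 5–6%.
- The correlations and regressions have no within-subject term. The consequence is about 7–19% error for a 5% correlation test if visits are pooled (assumed ICC 0.3–0.8), or three times as many tests if visits are analysed separately. The document does not say which.
- LPS, serotonin and BDNF get no adjusted test against diversity, and CRP is named in no analysis step. This follows from the text and needs no assumption.

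The primary hypothesis ("can be detected using a one-sided test of the primary hypothesis that cancer survivors will have lower alpha diversity relative to controls") and its power are untouched.

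**What to change.** In Data analysis, Objectives 2 and 3, replace the screen-then-regress step:

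1. For every outcome in hypotheses (ii) and (iii), naming CRP, LPS, serotonin and BDNF explicitly, fit one pre-specified LMM in survivors. Fixed effects are diversity, time, the theory-based covariates already listed, and age; add a subject random intercept.
2. Drop entry by significance. If diet, smoking or another recorded factor is considered a confounder, name it in advance.
3. Keep the univariate correlations as descriptive.
4. Optionally, control the false discovery rate within each objective.

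**Cost.** Wording only: the plan already uses an LMM, and the data are already to be collected. There will be fewer nominally significant associations and somewhat wider intervals. The covariate list must stay short. With one coefficient per covariate, the model has 1 (diversity) + 2 (time) + 7 + 1 (age) = 11 fixed effects besides the intercept, for about 50 people. Any added confounder should preferably replace a less important covariate.

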**Fig. 1 Fig1:**
[figure not shown]
Chemotherapy Driven Dysbiosis of the Microbiota-Gut-Brain Axis. The Chemotherapy Driven Dysbiosis of the Microbiota-Gut-Brain Axis model posits that chemotherapy given to young cancer patients induces long-term gut dysbiosis, increasing intestinal permeability (i.e. “leaky gut”), which allows bacterial toxins, such as lipopolysaccharide (LPS), to enter the blood stream. This subsequently leads to systemic inflammation via increases in pro-inflammatory cytokines, especially IL-6, IL-1b, and TNF-a, and C-reactive protein, as well as dysregulation of the HPA-axis. This creates a feedback loop in which inflammatory mechanisms trigger the stress response to increase systemic cortisol, feeding back into the immune system to exacerbate levels of inflammation. Gut microbiota dysbiosis and dysregulation of the immune system and HPA-axis attenuate levels of serotonin (5-HT) and brain derived neurotrophic factor (BDNF), which then work in tandem to induce changes in psychological and cognitive function, including increased symptoms of anxiety and depression (i.e. “sickness behaviours”), pain, fatigue, and social and cognitive deficits. Finally, gut dysbiosis, immune, and HPA-axis dysregulation may also augment patients’ vulnerability to increased adipose tissue, and subsequent overweight and obesity, further compromising their health

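### Objectives 2 and 3: the rule for adding correlated variables admits markers that Figure 1 places on or below the gut pathway, so the adjusted gut coefficient is not the overall association that hypotheses (ii) and (iii) state

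*Protocol article*

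**What the plan says.** All references are to the protocol article.

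- **Hypotheses (Present study).** Hypothesis (iii) reads: "Gut dysbiosis will be associated with increased anxiety, depression, PTSD symptoms, pain, fatigue, and social and cognitive deficits in survivors". Hypothesis (ii) is worded in the same way for overweight, inflammatory markers, LPS, serotonin, BDNF and cortisol. Both concern association with gut dysbiosis. Neither is restricted to the part that bypasses a particular marker.
- **Objective 3 (Data analysis).** Screening comes first: "We will test the relationships between gut microbiota, 5-HT and BDNF, and cognitive and psychological parameters using univariate correlations". The models that follow are described as "regressing psychological and cognitive parameters on gut microbiota diversity will be conducted, including variables that showed significant univariate correlations in the modelling".
- **Objective 2 (Data analysis).** Screening is done by "examining associations between the gut microbiota, cytokines, LPS, 5-HT and BDNF, cortisol, and body composition using univariate correlations". The models are then described as "regressing cytokines, cortisol and body composition on gut microbiota diversity will be conducted, including variables that showed significant univariate correlations in the modelling".
- **Theory-based covariates (Data analysis).** A separate sentence lists diagnosis type, mucositis history, glucocorticoid, antibiotic and probiotic use, birth delivery mode and breastfeeding. No serum marker or cortisol is among them.
- **Causal model (Fig. 1 legend).** Dysbiosis raises permeability and lets LPS into the blood, which raises cytokines and CRP and dysregulates the HPA axis. Then: "Gut microbiota dysbiosis and dysregulation of the immune system and HPA-axis attenuate levels of serotonin (5-HT) and brain derived neurotrophic factor (BDNF"). For the last step, the two are said to "attenuate levels of serotonin (5-HT) and brain derived neurotrophic factor (BDNF), which then work in tandem to induce changes in psychological and cognitive function". Gut dysbiosis itself, alongside immune and HPA dysregulation, is named as a contributor to adipose tissue.
- **Mediation.** No mediation or indirect-effect analysis is described, although the Discussion says the study will allow aspects of this model to be explored and validated.

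**The concern.** A variable that carries the effect of an exposure is not a confounder of it. If serotonin and BDNF transmit the gut effect on mood, then holding them fixed leaves only the part of the effect that goes another way. That is a legitimate quantity, but it is not the one in hypothesis (iii). A variable that lies below the outcome is worse: conditioning on it distorts the exposure coefficient and isolates no effect at all.

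The entry rule aggravates this, because a marker enters when it correlates significantly with the outcome. If the proposed pathway is real, the marker is likely to enter and the gut coefficient to shrink. The problem is separate from selection by p-value; it would remain if the same markers were pre-specified as covariates.

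At stake is how the two main secondary hypotheses are read. A reader who sees a crude gut association beside a null adjusted coefficient may conclude that it was confounding, when the data in fact agree with Figure 1.

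**Working it through.** **1. The plan's own figure.** Sample size and power gives 50 per group for d = 0.5, one-sided alpha 0.05, power 0.80. n = 2 × (1.645 + 0.842)² / 0.5² = 49.5, so 50 per group; it reproduces. It concerns the primary alpha-diversity comparison only. No figure is given for the Objective 2 and 3 regressions.

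**2. Which markers the rule can admit, and their place in Figure 1.**

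| Outcome | Screened markers | Place in Figure 1 |
|---|---|---|
| Psychological, cognitive (Obj. 3) | 5-HT, BDNF | on the path from gut to outcome |
| Cytokines (Obj. 2) | LPS | on the path |
| Cytokines, cortisol (Obj. 2) | 5-HT, BDNF | downstream of the outcome |
| Body composition (Obj. 2) | LPS, cytokines, cortisol | on the path, beside a gut path of its own |

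**3. Objective 3, one mediator.** Let G be gut diversity, M the marker and Y the outcome, all with unit variance: M = aG + error and Y = bM + cG + error.
- Without M, the coefficient of G is ab + c (overall association).
- With M, it is c (direct effect).

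The values of a, b and c are assumptions. n = 50 because the hypotheses concern survivors. M enters if its correlation with Y has p < 0.05. Significance percentages are simulated.

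| a, b, c | Without M: ab + c | Significant | With M: c | Significant under the rule |
|---|---|---|---|---|
| 0.5, 0.5, 0 (full mediation) | 0.25 | 42% | 0.00 | 5% |
| 0.6, 0.6, 0 (full mediation) | 0.36 | 74% | 0.00 | 6% |
| 0.5, 0.4, 0.15 (partial) | 0.20 + 0.15 = 0.35 | 71% | 0.15 | 18% |
| 0.3, 0.3, 0.2 (partial, weaker) | 0.09 + 0.20 = 0.29 | 54% | 0.20 (mean 0.21 under the rule) | 32% |

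In the first row the marker enters in 97% of runs. Repeat simulations moved these percentages by no more than about two points.

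**4. Two mediators (5-HT and BDNF), n = 50.**
- Full mediation, each path 0.5 then 0.4: the overall coefficient is 2 × 0.5 × 0.4 = 0.40, significant in 84%. Under the rule it is about 0 and 6%.
- Half the effect direct (0.5 then 0.2, direct 0.2): 0.40 falls to 0.21, and 83% to 28%.

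If controls were pooled (n = 100), paths 0.3 then 0.3 with direct 0.2 give 0.38 falling to 0.20, and 98% falling to 58%.

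**5. Objective 2, cytokine outcome C.**
- *LPS (L) on the path*, gut–LPS 0.5 and LPS–cytokine 0.5. Then cov(G,C) = 0.25, cov(G,L) = cov(L,C) = 0.5. Adjusted for L, the gut coefficient is (0.25 − 0.5 × 0.5) / (1 − 0.5²) = 0, against 0.25 unadjusted.
- *Serotonin (S) downstream*, S = 0.4G + 0.4C + 0.7 × error. Var(S) = 0.16 + 0.16 + 2 × 0.16 × 0.25 + 0.49 = 0.89; cov(S,G) = 0.4 + 0.4 × 0.25 = 0.5; cov(S,C) = 0.4 × 0.25 + 0.4 = 0.5. Adjusted for S, the gut coefficient is (0.25 × 0.89 − 0.5 × 0.5) / (0.89 − 0.25) = −0.0275 / 0.64 = −0.04. A true 0.25 changes sign. Nothing has been mediated here; this is bias from conditioning on a consequence of the outcome.

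**The case against.** **The crude association is already planned.** This stands. Both objectives correlate gut microbiota with the outcomes before any regression, and the hypotheses say only that there will be an association. A reader might infer that the planned regressions would make hypotheses (ii) and (iii) look refuted; the documents do not support that, because the mediator-free correlation is reported alongside. What it lacks is adjustment for antibiotics, mucositis, diagnosis type and the other listed covariates. The plan describes no estimate that is both adjusted for confounders and free of these markers.

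**The coefficient need not vanish.** This also stands. It does so only if the whole effect runs through the admitted markers, and the article does not claim that. Figure 1 names dysbiosis itself among the contributors to adipose tissue, and the Background mentions vagal routes and unmeasured neurotransmitters. Attenuation is the general result.

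**The text does not name the variables that enter.** True, and a condensed article may leave exact model terms to a fuller plan. But in Objective 3 serotonin and BDNF are the only screened variables other than gut microbiota and the outcomes, and the theory-based covariates have a sentence of their own. The markers are the natural referent, and the rule as stated conflicts with Figure 1.

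**Not every marker is a mediator for every outcome.** Correct. LPS and cytokines are not screened in Objective 3, and serotonin and BDNF are not mediators for cytokines or cortisol. The table by outcome above respects this.

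**The study is exploratory.** The Discussion says so. That lowers the severity but does not make a direct-effect coefficient a test of an overall association.

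**Conclusion.** The point holds in a limited form. On its natural reading, the entry rule puts on-path or downstream markers beside gut diversity, and the resulting coefficient does not estimate what hypotheses (ii) and (iii) state.

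In the one-mediator examples with 50 survivors, the size runs from moderate attenuation (0.29 to about 0.21; 54% to 32% significant), through strong attenuation (0.35 to 0.15; 71% to 18%), to loss of the coefficient under full mediation (0.25 to about 0; 42% to 5%). All of these rest on assumed standardised paths, markers measured without error, a single time point and linear effects. The direction follows from Figure 1; the size cannot be known from the documents.

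The likely practical result is a positive crude correlation beside a weak or null adjusted coefficient, open to being misread as confounding. The primary hypothesis on alpha diversity, its sample size and the data collection are untouched. This is a should-fix.

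**What to change.** 1. State that hypotheses (ii) and (iii) are tested by the gut-diversity coefficient from a model containing gut diversity and the theory-based covariates already listed under Data analysis.
2. For each outcome, exclude from that model any of 5-HT, BDNF, LPS, cytokines and cortisol that Figure 1 places on or below the path to it: 5-HT and BDNF for psychological and cognitive outcomes; LPS, 5-HT and BDNF for cytokines; 5-HT, BDNF and any marker upstream on the gut path for cortisol; LPS, cytokines and cortisol for body composition.
3. Replace the rule that admits whatever correlates with a fixed list per outcome.
4. Report any model that adds mediators as a separate second step, labelled exploratory mediation, with the indirect effect and a bootstrap interval. Do not call models that condition on markers below the outcome mediation models.

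Cost: a change of wording and one extra model per outcome. No new data, visits or participants are needed.
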